## Abstract

**Introduction:**

Oral anticoagulants (OACs) are first-line drugs for stroke prevention in patients with atrial fibrillation (AF). The introduction of new lines of therapy with direct oral anticoagulants (DOACs) has led to a decreased use of vitamin K antagonists (VKAs). Comparative analyses of DOACs in clinical trials are scarce and the comparator has mostly been warfarin. Their impact on health outcomes in observational studies has not always been consistent. The aim of this study is to evaluate the effectiveness and safety of DOACs and VKAs in patients with AF using Real-World Data (RWD).

**Methods and analysis:**

Population-based retrospective cohort study using RWD from actual practice. Period: January 2012-December 2020. Inclusion criteria: patients with AF who had not taken OACs in the previous 12 months. Exclusion criteria: <40 years, with severe mitral stenosis, or valvular heart disease or aortic and/or mitral valve procedures. Data source: The Andalusian Population Health Database, Spain. Outcome measures: a) Effectiveness: ischaemic stroke, transient ischaemic attack, systemic and pulmonary embolism, and death; b) Safety: gastrointestinal and intracranial haemorrhaging; Independent variables: age, sex, comorbidities, medication and health resource use, CHA_2_DS_2_-VAS_C_, HAS-BLED, and analytical tests. Statistical analysis: crude incidence analysis, survival models, Kaplan-Meier, Cox regression analysis adjusted for possible confounding and paired analysis by propensity score matching.

## Introduction

Atrial fibrillation (AF) is the most common type of cardiac arrhythmia and the main cause of thromboembolic strokes and systemic embolism [1, 2]. Antithrombotic drugs are a cornerstone of the management of this disease. The treatments recommended by clinical practice guidelines for the prevention of strokes are oral anticoagulants (OAC), which include vitamin K antagonists (VKA) (warfarin and acenocoumarol) and the new direct anticoagulants (DOAC) (dabigatran, rivaroxaban, apixaban and edoxaban) [3, 4]. In recent years, however, DOAC prescriptions have largely replaced those of VKAs.

Clinical trials evaluating the efficacy and safety of DOACs have mostly used warfarin as a comparator drug [5–8]. A meta-analysis of clinical trials showed that DOACs reduce stroke, intracranial haemorrhage and mortality [9].

Nevertheless, different observational studies based on Real-World Data (RWD) have provided new evidence regarding the comparative safety and effectiveness of these drugs. Their findings are not always consistent. In a Danish cohort [10], Nielsen *et al*. found no significant differences in the effectiveness and safety profile of DOACs versus warfarin, except for dabigatran, which was associated with less bleeding. Lip *et al*. [11] showed, in patients with AF and high risk of gastrointestinal bleeding, that DOACs were associated with lower rates of vascular stroke and systemic embolism but had varying risks of major bleeding compared with warfarin. These results were similar to those obtained by Sheth *et al*. [12].

Other observational studies have compared the effectiveness and safety of different DOACs. Durand *et al*. [13] conducted a meta-analysis and found that patients on apixaban showed a lower risk of stroke and bleeding versus rivaroxaban, and similarly versus dabigatran. Ingason *et al*. [14] concluded that rivaroxaban was associated with an increased risk of gastrointestinal bleeding compared to dabigatran and apixaban. Acenocoumarol is the most widely used VKA in countries like Spain and Portugal, and has not been evaluated in clinical trials. Rodríguez-Bernal *et al*. have studied the effectiveness and safety profile of DOACs against acenocoumarol. They found no differences in clinical outcomes between DOACs and acenocoumarol overall, except in the case of intracranial haemorrhage, where the risk was lower with dabigatran and rivaroxaban than with acenocoumarol [15].

Acenocoumarol and warfarin have different half-lives and it is not known how this may affect outcomes in RWD studies. Dalmau *et al*. [16] found there was no association between poor anticoagulation control and the type of VKA treatment administered. Besides that, a new DOAC, edoxaban, came on to the market and it has not been included in RWD studies. The objective of the study is to evaluate the comparative effectiveness and safety of acenocoumarol, warfarin, dabigatran, rivaroxaban, apixaban and edoxaban in patients diagnosed with AF under routine clinical practice.

## Methods and analysis

### Study design

This is an observational retrospective cohort study of regionwide population of all patients with atrial fibrillation, who were newly prescribed an OAC: acenocoumarol (reference treatment), warfarin, dabigatran, rivaroxaban, apixaban, or edoxaban.

### Population and setting

The study will be carried out in the region of Andalusia, where the Public Health System of Andalusia) (PHS-A) provides health coverage to a population of 8.4 million inhabitants.

The patients in the study will be those seen in consultations at any level of health care of the PHS-A (primary care and hospital) between January 2012 and December 2020 (Fig 1) who meet the following inclusion/exclusion criteria:

**Fig 1 pone.0294822.g001:**
[figure not shown]
Patient selection criteria.

Inclusion criteria (S1 Table):

Diagnosis of AF or atrial flutter.Individuals initiating treatment with OACs under routine clinical practice conditions (*naive* population). Only new users of OAC (incident cases) will be included, even if they have taken OAC in the past, provided they stopped taking it during the 12 months prior to inclusion in the study. Patient data from 2012 onwards will be used.

Exclusion criteria (S1 Table):

Under 40 years of agePatients with severe mitral stenosisPatients with valvular heart diseasePatients undergoing aortic and/or mitral valve procedures.

This is a pathology that tends to present, in the majority of cases, after the age of 40 years [5–8, 15]. By selecting patients > 40 years, we consider that the conclusions for the majority adult population, which is the target population of our study, would gain in homogeneity.

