A significance level of 0.15 will be used in preliminary univariate analysis to enable the selection of variables for inclusion in multivariate analysis. Once these variables have been selected, a multivariate analysis will be performed to select the final model. The analysis will be performed for both effectiveness and safety events. HRs and 95% confidence intervals (95% CIs) will be calculated for the selected variables once the application requirements have been validated.

The characteristics of the total study population and of each of the cohorts based on the first OAC used will be reported in the corresponding tables as percentages, means (standard deviation) or medians (interquartile range). Incidence rates will be calculated as the number of events divided by the corresponding denominator of person-time in follow-up.

Intention-to-treat analysis will be carried out by categorising each patient according to the first anticoagulant treatment they start taking in the study period, provided that they have not taken any other anticoagulant for at least 12 months previously (“washout period”) and regardless of any possible changes in type of anticoagulant or non-adherence that may occur in the follow-up period (Fig 3).

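### As written, the 12-month washout and baseline look-back cannot be fully observed for patients who start an anticoagulant in 2012, so some ongoing users could be counted as new users

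*Protocol article*

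**What the plan says.** The relevant statements are in several sections of the protocol article.

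- **Abstract, Methods and analysis:** "Period: January 2012-December 2020. Inclusion criteria: patients with AF who had not taken OACs in the previous 12 months".
- **Population and setting:** patients are those seen at any level of care "between January 2012 and December 2020 (Fig 1) who meet the following inclusion/exclusion criteria".
- **Population and setting, inclusion criteria:** past OAC users may enter "provided they stopped taking it during the 12 months prior to inclusion in the study". The next sentence reads "Patient data from 2012 onwards will be used".
- **Data analysis plan:** each patient is classified by the first OAC begun within the study window. The washout is attached as a condition: "provided that they have not taken any other anticoagulant for at least 12 months previously".
- **Outcome measures:** time zero is the first pharmacy dispensing. CHADS2, CHA2DS2-VASc and HAS-BLED are scored at inclusion from the preceding 12 months of records.
- **Limitations:** because the DOACs were launched at different times, follow-up will be defined from when the drugs were marketed. No dates are given.

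The text shown mentions no 2011 extract for look-back, no 2013 start for index dates, and no minimum observed history before the index date.

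**The concern.** A new-user design needs a period in which earlier use would have been seen had it occurred. If records begin when recruitment begins, the first year of recruits does not have one. A patient on long-term treatment who collects a routine refill in January 2012 looks the same in the data as a patient starting that day.

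Such patients would fall mainly in the acenocoumarol and warfarin cohorts, since the Introduction describes DOACs as having displaced VKAs only in recent years. Acenocoumarol is the reference for all five planned comparisons, so an error in who belongs to that cohort can carry into each of them. Ongoing users have already survived and tolerated the early part of treatment, and their follow-up would start late.

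The baseline scores share the problem. Patients starting in 2012 would be scored on a shorter window than later starters. The Data analysis plan lists CHA2DS2-VASc, HAS-BLED and previous ischaemic and bleeding events as potential confounders, and it relies on propensity score matching on baseline characteristics. Matching cannot repair a wrong new-user label. It would also compare patients on covariates measured over unequal windows.

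**Working it through.** The protocol article gives no figure to reproduce here. The main check is calendar arithmetic.

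**Inputs from the document**
- Study and selection window: January 2012 to December 2020, which is 9 × 12 = 108 months or 3288 days.
- Required OAC-free period and score look-back: 12 months each.
- Earliest data, as written: 1 January 2012.

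**Observable look-back = index date − 1 January 2012**

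| First dispensing | Observable look-back |
|---|---|
| 1 January 2012 | 0 days |
| 1 April 2012 | 91 days |
| 1 July 2012 | 182 days |
| 31 December 2012 | 365 days |

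- Starts spread evenly over 2012: mean look-back = (0 + 365)/2 = 182.5 days, and 182.5/365 = 50% of the required year.
- Share of the window affected: 366/3288 = 11.1% of days.
- Left if index dates begin on 1 January 2013: 108 − 12 = 96 months, and 96/108 = 88.9%.

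The shortfall is not uniform. Continuing users on regular refills would show their first visible dispensing in the first weeks or months of 2012, so misclassification would concentrate there.

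**Illustration of possible size (assumed values, none from the document)**

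Let VKA starts be constant at n per year for 9 years. Let D be the mean duration of VKA use in years, so that in steady state D × n patients are on treatment on 1 January 2012. Let f be the fraction of them admitted as new.

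- Share of apparent VKA starters over the whole period = Df/(Df + 9)
- Share of apparent VKA starters in 2012 = Df/(Df + 1)

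| D (years) | f | Whole period | 2012 only |
|---|---|---|---|
| 1 | 0.1 | 0.1/9.1 = 1.1% | 0.1/1.1 = 9.1% |
| 2 | 0.5 | 1/10 = 10% | 1/2 = 50% |
| 4 | 1.0 | 4/13 = 30.8% | 4/5 = 80% |

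The range, about 1% to 31% over the whole period, is too wide to serve as an estimate. It shows that the effect could be negligible or substantial depending on quantities the document does not give. It also describes the cohorts before matching, not the matched sets in which treatments are compared.

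**The case against.** **The dates may be settled elsewhere.** The sentence on data from 2012 does not contain the word *only*, and the selection window is phrased in terms of when patients were seen, not when the first index dispensing may fall. The team may intend 2012 as a run-in year, or may draw earlier dispensing records for the washout. Figs 1 and 3 and S1 Table are not shown and could say so. This stands as a limit on certainty: entry of ongoing users is what the written dates would allow, not something the document says will happen. It does not remove the point. The visible text fixes a data start that conflicts with the washout, and it classifies patients by the first OAC started anywhere in the study period.

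**A reader might infer that the DOAC hazard ratios are biased against the DOACs.** Survivorship among ongoing users would tend to favour acenocoumarol. But if risk is under-recorded for 2012 entrants, acenocoumarol patients who are sicker than they appear could be matched to healthier DOAC patients, which works the other way. The document gives no basis for a net direction. Nor is under-recording certain for each patient: look-back is shortened, not absent, age and sex need none, and chronic conditions may be recorded again within a shorter window.

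**A reader might infer that every DOAC comparison is affected.** The Limitations section's commitment on follow-up after launch may reduce the problem for later-marketed DOACs, if acenocoumarol comparators are restricted to the same calendar period. The text does not say how the restriction is applied, and it does nothing evident for warfarin versus acenocoumarol.

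**A reader might put ongoing users at 18% to 50% of the VKA cohort.** This results from assuming 2 to 6 years' mean use, 6 to 9 years of accrual and admission of every ongoing user: 2/(2 + 9) = 18% and 6/(6 + 6) = 50%. None of those inputs is in the document.

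**Conclusion.** The point holds as a conflict between stated dates. With selection from January 2012, a 12-month washout and patient data from 2012 onwards, neither the washout nor the 12-month score look-back can be fully observed for 2012 starters, who occupy 11.1% of the calendar window. Observable history runs from 0 days to about a year and averages half of what is required.

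Patients already on treatment could therefore be misclassified as new users, mainly in the acenocoumarol and warfarin cohorts, and the planned matching would not correct this. The conclusion assumes that 2012 is the true start of the usable data and that index dates are accepted from January 2012. Both are the natural reading of the text, but the unshown figures and S1 Table could qualify them. The net direction and size of any bias, and how many comparisons it reaches, cannot be established from the document. The correction is still warranted, because new-user status underlies every comparison.

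**What to change.** State one of the following in Population and setting, and carry it through to the Data analysis plan:

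1. Dispensing and diagnosis data for 2011 are extracted and used for look-back only (washout and baseline scores). All 108 months of index dates are kept.
2. The first eligible index date is 1 January 2013, and 2012 serves as look-back only. This keeps 96 of 108 months (88.9%).

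In both cases, require at least 12 months of observable history before the index date for every patient. If Fig 1, Fig 3 or S1 Table already applies one of these rules, the sentence on data from 2012 should be reworded to agree.

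Option 1 costs one more year of data extraction. Option 2 costs the 2012 initiators, who are probably mostly VKA users, and shortens the longest possible follow-up by a year. It needs no new data.

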### Data sources

The data source will be the Andalusian Population Health Database (APHD) [17]. This is a population-based health information system that collects clinical data and data on the use of health resources for each individual receiving health care in the Andalusian Health Service. This information is held in different databases that are linked by the unique health history number of each patient in the PHS-A (Fig 2):

**Fig 2 pone.0294822.g002:**
[figure not shown]
Data sources and linkage between databases. PHS-A: Public Health System of Andalusia; ICD: International Classification of Diseases. User database contains the patient’s affiliation and socio-demographic data. Database on resource use and/or admissions for outpatient consultations, primary care, hospital care and emergencies. Database containing prescription and pharmacy dispensing data in primary and hospital care. Clinical tests database.

The information will be extracted from the databases and transferred to a single file for analysis by the Excel, R and Stata statistical programmes. Patients will be anonymised for evaluation by the study investigators.

### Outcome measures

The pre-specified effectiveness outcomes will be the incidence of new diagnosis among the following list: transient ischaemic attack, systemic embolism, pulmonary embolism, ischaemic stroke and all-cause mortality, as a combined effectiveness endpoint.

Safety outcomes will be the incidence of new diagnosis of major haemorrhages leading to hospital admission (gastrointestinal and intracranial haemorrhages). They will be considered as a combined safety endpoint. Post-traumatic bleeding will be excluded.

All effectiveness and safety events will be associated with their dates of onset and identified using the corresponding International Classification of Diseases (ICD-9 or ICD-10 codes) (S2 Table).

Time-to-event will be defined as the number of days elapsed from the date of initiation of treatment (dispensing at pharmacy) until the date of the event, death or the end of study period (December/2020).

The following independent variables will be analysed according to relevance and availability in PHS-A databases:

Type of OACs: date of start and end of treatment and dosages of the OACs under study (DOACs and VKA) will be collected.Sociodemographic data: age (time between date of birth and the event), Health Management Area, reference hospital, province.Contacts with the PHS-A (episode count and attendance indicators recorded in the last year and the annual average recorded during the study period) in primary care centres, hospitals, at home, and in the emergency department.Comorbidities: diagnosed health problems and their associated dates will be included (S3 Table). Comorbidity will be defined as the presence of an active diagnosis in the available databases (emergency, hospital and primary care) in the 12 months prior to the date of the event.Variables related to medication use: dates of start and end of treatment, dosage. The use of medication related to increased risk of bleeding or prevention of bleeding will be analysed according to the Anatomical Therapeutic Chemical (ATC) classification of the WHO Collaborating Centre for Drug Statistics Methodology (www.whocc.no/) (S4 Table).CHADS_2_ and CHA_2_DS_2_-VAS_C_ (Thromboembolic Risk Assessment) and HAS-BLED (Bleeding Risk Assessment) scales: the scores on these scales will be calculated at the date of the patient’s inclusion in the study, using the information available in the previous 12 months.All variables or diseases included in the CHADS2 and CHA2DS2-VASC scores will be considered for calculation of the total thromboembolic risk score. Diagnoses of “previous stroke”, “ischaemic stroke” (excluding haemorrhagic stroke), “TIA”, "systemic embolism", "pulmonary embolism" (hospital care diagnoses) and “thromboembolic events” (primary care diagnoses) will be grouped into a single section of the CHA2DS2-VASC scores. A history of “myocardial infarction", "angina pectoris" and "peripheral arterial disease" (diagnoses recorded in both hospital and primary care) will be considered as "vascular disease". The total score of the scale will be between 0 and 9 points.Intracranial haemorrhages and haemorrhagic strokes will be counted as "previous cerebrovascular accident" on the HAS-BLED Scale. Records with an ICD-9 or ICD-10 identification for renal or liver failure, or their primary care equivalents, will be collected. Safety outcome events of the study (intracranial or gastrointestinal haemorrhage) previously experienced by the patient will be considered as “Previous history of or predisposition to bleeding". "Labile INR" will not be included in calculations on this scale, since it applies to just one of the groups of medicines under study (VKA). Drugs predisposing to bleeding will be included in the calculation of bleeding risk (S4 Table). The “alcohol consumption” variable will not be included in the scale, as this information is not available in the vast majority of cases. The total score of the scale will be between 0 and 7 pointsPredictor variables will be analysed for associations with events based on information available in the previous 12 months.

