There are other limitations. It is assumed that the medication dispensed is the medication that is taken by the patient, as it has been considered by other investigators [10, 13, 14, 16] but it cannot be rule out residual confounding. There may however be cases in which the patient obtains medication without a prescription or in a different region from the one in which the study is being conducted (Andalusia). It is not possible to record other medications with a bleeding risk that the patient may be taking that do not require a prescription (such as Aspirin®). However, the use of acetylsalicylic acid will be analysed, and other use of this drug is not expected to have a direct impact on the analysis. Socio-economic status will not be assessed since this data is barely reflected in the clinical records of patients. However, given that DOACs are subject to approval for the indication of non-valvular AF and that this is a universal public health service, socioeconomic status is not expected to affect the selection of type of anticoagulant. Finally, the analysis will be conducted in a particular region in southern Spain and may not extrapolate to other populations.

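### Follow-up does not end when a patient leaves the Andalusian health system, so incidence rates are biased down and event-free curves up

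*Protocol article*

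**What the plan says.** The time-to-event definition under Outcome measures starts the clock "from the date of initiation of treatment (dispensing at pharmacy") and runs it "until the date of the event, death or the end of study period (December/2020"). These are the only end points given, and no other section of the article adds one.

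Under Data sources, the database is described as one that "collects clinical data and data on the use of health resources for each individual receiving health care in the Andalusian Health Service".

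Under Data analysis plan, "Incidence rates will be calculated as the number of events divided by the corresponding denominator of person-time in follow-up". Kaplan-Meier curves and Cox models are planned on the same times. Patients are analysed by their first anticoagulant, "regardless of any possible changes in type of anticoagulant or non-adherence that may occur in the follow-up period", so the end of dispensing does not stop the clock either.

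The study period is "between January 2012 and December 2020", so follow-up can last about nine years. The Fig 2 legend says that the user database holds the patient's "affiliation and socio-demographic data". The Limitations section mentions patients who get medication "in a different region from the one in which the study is being conducted", but it does not discuss outcomes that occur elsewhere or loss of follow-up.

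**The concern.** The rule for ending follow-up and the reach of the data source do not match. A stroke, embolism or admission for bleeding treated outside the Andalusian service does not reach the database, but the patient's time at risk continues to accrue. That time can add nothing to the numerator of a rate and everything to its denominator. In a Kaplan-Meier analysis the same patients stay in the risk set as apparent survivors.

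The error has a known direction and grows with time since treatment start. The Strengths section presents long follow-up as an advantage, and the late parts of the curves are where the error is largest. Absolute rates and survival curves are planned outputs, so a reader would take them at face value.

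**Working it through.** The article states no event rate, exit rate or event count, so there is no figure of its own to reproduce. The check is an illustration with stated assumptions.

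**Inputs from the article:** the end-of-follow-up rule (Outcome measures), capture limited to the Andalusian service (Data sources), person-time as denominator (Data analysis plan), and a window of nine years (Population and setting).

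**Assumptions:** constant event rate L (5% per year; 2% and 10% also tried), constant exit rate m (0.5% to 3% per year), exit independent of the event, and nothing seen after exit.

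**Formulas.** Let a = L + m and let T be the time from treatment start to the end of the study.
- Person-time if censored at exit: P1 = (1 − e^(−aT))/a
- Events seen: E = L × P1
- Person-time under the stated rule: P2 = T − (L/a)(T − P1)
- Observed rate divided by true rate: (E/P2)/L = P1/P2

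**Worked case:** L = 0.05, m = 0.02, T = 9.
- a = 0.07 and e^(−0.63) = 0.5326, so P1 = 0.4674/0.07 = 6.677 years.
- E = 0.05 × 6.677 = 0.334.
- P2 = 9 − (0.05/0.07)(9 − 6.677) = 7.341 years.
- Ratio = 6.677/7.341 = 0.910, so the rate is understated by 9.0%.
- Event-free share at nine years: true value e^(−0.45) = 0.638; under the stated rule 1 − 0.334 = 0.666.

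**Observed rate divided by true rate, L = 5% per year.** The last two columns spread entry evenly over a window of that length.

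| Exit per year | T = 2 y | T = 5 y | T = 9 y | 5-y window | 9-y window |
|---|---|---|---|---|---|
| 0.5% | 0.995 | 0.987 | 0.976 | 0.992 | 0.985 |
| 1% | 0.990 | 0.974 | 0.953 | 0.983 | 0.970 |
| 2% | 0.980 | 0.950 | 0.910 | 0.967 | 0.941 |
| 3% | 0.970 | 0.926 | 0.869 | 0.951 | 0.913 |

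Over the nine-year window the understatement is 1 − 0.985 = 1.5% to 1 − 0.913 = 8.7%. The event rate hardly matters: at 3% exit, the nine-year-window ratio is 0.915 for L = 2% and 0.911 for L = 10%.

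**Between-drug contrasts.** A simulation used 40,000 patients per group, entry over nine years for the reference and five for the comparator, a reference event rate of 5% per year and a true hazard ratio of 0.80.

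| Exit, reference / comparator | Measure | Censored at exit | Stated rule |
|---|---|---|---|
| 2% / 2% | Crude rate ratio | 0.800 | 0.822 |
| 2% / 2% | Cox hazard ratio | 0.804 | 0.805 |
| 3% / 1% | Crude rate ratio | 0.809 | 0.873 |
| 3% / 1% | Cox hazard ratio | 0.808 | 0.839 |

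With equal exit, the Cox model compares patients at the same time since start, when nearly the same fraction of each risk set has left, so the error almost cancels. It does not cancel when exit differs by drug.

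**The case against.** The strongest reply is that a one-sentence definition in a condensed article need not be complete, and that handling of patients who leave may sit in a fuller document. The sentence does not say that patients who leave stay at risk. This has some force. But the article gives a definite list of end points, and applying that list gives the wrong denominator. It is a stated rule to correct, not a topic left open.

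A reader might infer that comparisons between drugs are distorted because acenocoumarol has longer follow-up than the later drugs. The documents do not support that as a general statement. The Limitations section plans matching and a follow-up period defined from when the drugs were marketed. If windows are aligned within each comparison and exit is equal, the differential part largely disappears. The article gives no marketing dates, so the unequal windows in the simulation are assumed. The planned treatment contrast is a Cox hazard ratio, which hardly moves under equal exit, and nothing in the article suggests that leaving depends on the drug.

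A reader might also infer that recent arrivals already on treatment would pass as new users. The article states a 12-month washout, and the detailed selection criteria (Fig 1, S1 Table) are not visible. Any enrolment requirement may be there, so this is not part of the point.

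Two further limits stand. The article says the system serves the vast majority of the population, so exit may be rare, in which case the bias is small. If deaths outside the region reach the database, the mortality component is less affected; the article does not say whether they do.

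**Conclusion.** The point holds for absolute measures. Under the stated rule, incidence rates are biased down and Kaplan-Meier event-free curves up, increasingly so with longer follow-up. The size depends on an exit rate that the article does not give: about 1.5% to 9% understatement for an assumed 0.5% to 3% per year with entry spread over nine years, if exit is independent of the event and no outcome is seen after it.

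For hazard ratios the point is conditional: almost no effect with equal exit between drugs, and bias only if exit differs by drug. Any between-drug distortion of crude rates depends on whether follow-up windows are aligned as the Limitations section suggests. The correction is worth making because the direction is known and the change is small.

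**What to change.** In the time-to-event definition under Outcome measures, end follow-up at the earliest of event, death, end of PHS-A affiliation and 31 December 2020. Take the affiliation end date from the user database, and report the number and timing of exits by drug so that readers can judge whether exit differs.

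The Fig 2 legend shows that affiliation data are held but not that end dates are recorded, so the sponsor should confirm this. If they are not held, run a sensitivity analysis that censors at the last recorded contact or dispensing. That should not become the main analysis, because it also removes genuine event-free time from patients who are well and seldom seen.

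The cost is one sentence, one extra date field and slightly less person-time.
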